### Interim analyses {21b}

Trial Steering Committee will have access to interim results and make the final decision to terminate the trial. Interim analysis will take place in half-way of the trial.

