### Data management {19}

Only study investigators will have access to trial information and dataset. Personal information about enrolled participants will be collected in closed envelope in the hospital registry. Data will be held for 20 years after the trial. To protect confidentiality, no name/surname will be used. Each participant will be assigned a code number impossible to decode without a proper list. Participants will not be identified in the resulting manuscripts or reports. The Trial Steering Committee will have access to interim results and make the final decision to terminate the trial. Interim analysis will take place in half-way of the trial.

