## Statistical methods

### Statistical methods for primary and secondary outcomes {20a}

All statistical calculations will be performed using the statistical suite StatSoft Inc. (2014) STATISTICA (data analysis software system) version 12.0 (www.statsoft.com) and an Excel spreadsheet. Continuous variables will be characterized by arithmetic mean, standard deviation, median, minimum and maximum (range), and 95% CI (confidence interval). Qualitative variables, on the other hand, will be presented using the frequency and percentage values (percentage). The Shapiro–Wilk W test will be used to check whether the quantitative variable came from a normally distributed population. The Leven (Brown-Forsythe) test will be used to test the hypothesis of equal variances. Significance of differences between the two groups (model of unrelated variables) will be tested by the tests of significance of differences: Student’s *t*-test (or, in the absence of homogeneity of variance, the Welch test) or the Mann–Whitney U test (if the conditions of applicability of the Student’s *t*-test are not met or for variables measured on ordinal scale). Significance of differences between more than two groups will be checked by *F* test (ANOVA) or Kruskal–Wallis test (if the conditions of ANOVA applicability are not met). If statistically significant differences between the groups are obtained, post hoc tests will be used (Tukey’s test for *F*, Dunn’s test for Kruskal–Wallis). Chi-square tests of independence will be used for categorical variables (using Yates correction for cell counts below 10, checking Cochran conditions, Fisher’s exact test, respectively). In order to determine the relationship, strength, and direction between the variables, correlation analysis will be applied by calculating the Pearson and/or Spearman correlation coefficients. *P* = 0.05 will be assumed as the significance level in all calculations.

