The trial was planned as non-inferiority study with test power = 80%, *p*-value = 0.05, and threshold for clinical significance = 8%. A percentage loss of 10% was assumed. Recurrence rate was assumed to be 4% based on literature data. Based on those assumptions, minimal sample size in both arms was established at 83–102. To ensure sufficient participant numbers at completion of the trial, sample size was established at 204 participants. To maintain the integrity and clarity of our results, we chose to focus on our primary analysis. Given the focused nature of our primary research question and to maintain the power of our statistical analyses, we opted not to divide our sample further into subgroups.

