### Composition of the data monitoring committee, its role and reporting structure {21a}

Despite trial being a low-risk intervention, the Data Monitoring and Ethics Committee will convene biannually, or more frequently if emergent issues arise, to review trial conduct and ensure the safety and well-being of participants.

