## Trial status

Protocol version number and date: version 2.0 date 19/01/2023. Recruitment for the trial began in February 2023 and is expected to be completed by February–March 2024.

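### The half-way interim gives results and the power to terminate to a committee that includes the blinded outcome assessor, at a time that cannot support a useful early non-inferiority decision

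*Protocol article*

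**What the plan says.** Protocol article, Interim analyses {21b}: "Interim analysis will take place in half-way of the trial". Data management {19} says the same and adds: "The Trial Steering Committee will have access to interim results and make the final decision to terminate the trial". Neither section says what is counted to reach half-way, what is compared, on what grounds the trial may stop, or whether results are shown by arm.

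Study setting {9} and the section on the coordinating center and steering committee {5d} list the committee: Study Chief, Study Director, Study Secretary and two collaborators. Outcomes {12}, Participant timeline {13} and Who will be blinded {17a} have the Study Secretary make the 3- and 12-month telephone calls while blinded to the technique.

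A separate body exists. Under {21a}, "the Data Monitoring and Ethics Committee will convene biannually" to review conduct and participant safety. It is given no part in the interim.

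The primary endpoint is recurrence over one year. On timing, Trial status says "Recruitment for the trial began in February 2023 and is expected to be completed by" February–March 2024. On the error rate, {20a} closes its list of tests with "0.05 will be assumed as the significance level in all calculations". The sample size uses the same 0.05, 80% power, an 8% margin and 10% loss, and "Recurrence rate was assumed to be 4% based on literature data".

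**The concern.** Two features of the stated plan work against the trial.

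First, the person who ascertains the primary endpoint by telephone belongs to the body that receives interim results. If those results are by arm, the assessor learns which arm is doing worse while the remaining 12-month calls are still to be made. Recurrence is picked up by questioning and leads to an outpatient visit only where there is concern, so knowledge of the trend could affect who is called in. The other members run the trial or operate in it, and a trend could affect their conduct too.

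Second, the endpoint takes about as long to mature as the trial takes to recruit. A look placed half-way, on any natural definition, either precedes nearly all primary data or follows the end of recruitment. The committee could then end the trial on very few recurrences. If the look included a test against the margin at the general 0.05, it would also add to the chance of a false non-inferiority claim.

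**Working it through.** **1. The plan's own sample size.** Inputs from {14} and {20a}: 4% recurrence (taken for both arms), margin 0.08, power 80%, loss 10%.

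n per arm = (z_α + z_β)² × 2 × 0.04 × 0.96 / 0.08² = (z_α + z_β)² × 12.

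- One-sided 0.05: (1.645 + 0.842)² × 12 ≈ 74.2, so 75. With loss: 75 × 1.1 = 82.5, so 83; or 75 / 0.9 = 83.3, so 84.
- One-sided 0.025: (1.960 + 0.842)² × 12 ≈ 94.2, so 95. With loss: 105 or 106.

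The stated 83 therefore fits one-sided 0.05 and a single final test. The stated 102 does not follow exactly from these inputs, and the sidedness is not stated, so both levels are carried below. Neither calculation allows for a second look.

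**2. Data available at half-way.** Assumption: even accrual of 204 patients over R = 12, 13 or 14 months (the article gives only start and expected end), before any loss.

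Enrolled at month m = 204 × min(1, m/R). Twelve-month outcomes = 204 × (m − 12)/R, held between 0 and 204. Expected recurrences = 4% of those outcomes.

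| Meaning of half-way | Month (R = 12 / 13 / 14) | Enrolled | 12-month outcomes | Expected recurrences, both arms |
|---|---|---|---|---|
| Half of enrolment, m = R/2 | 6 / 6.5 / 7 | 102 | 0 | 0 |
| Half of calendar, m = (R + 12)/2 | 12 / 12.5 / 13 | 204 / 196 / 189 | 0 / 7.8 / 14.6 | 0 / 0.31 / 0.58 |
| Half of outcomes, m = 12 + R/2 | 18 / 18.5 / 19 | 204 | 102 | 4.08 |

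On the third reading, recruitment closed 12 − R/2 = 6, 5.5 or 5 months before the look. On the first, 51 to 58 patients have reached 3 months, so early data exist even though primary data do not.

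**3. What a test at half the outcomes could do.** With 2 recurrences among 51 in each arm, the standard error of the difference is √(2 × 0.0392 × 0.9608 / 51) = 0.0384. The Wald upper limit is 1.645 × 0.0384 = 6.3% (one-sided 95%) or 1.960 × 0.0384 = 7.5% (one-sided 97.5%). Both lie below 8%, so four recurrences in all could pass the margin.

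**4. Error rate if non-inferiority were tested at both looks.** The two statistics are taken as bivariate normal with correlation √0.5 = 0.707, each look at the nominal level. False non-inferiority rate = 1 − P(Z₁ < c and Z₂ < c).

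- c = 1.645: 5% becomes 8.0%.
- c = 1.960: 2.5% becomes 4.2%.

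Events are few, so this was checked by simulation: true rates 4% and 12%, Wald limits, 51 then 102 per arm. At one-sided 0.05 the final test alone gave 6.1% and either look 10.9%; at one-sided 0.025, 3.6% and 6.8%. Part of the excess over nominal comes from the Wald limits, but the rise from the first figure to the second is due to the extra look.

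**5. The blind.** Set side by side: the Study Secretary is a Steering Committee member ({9}, {5d}); the Steering Committee has access to interim results ({19}, {21b}); the Study Secretary is blinded for the calls ({12}, {13}, {17a}). The three statements are compatible only if the results are pooled, and the article does not say so.

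**The case against.** The strongest objection is that the interim test is assumed. Neither {19} nor {21b} mentions the margin or stopping for non-inferiority, and the 0.05 statement ends a generic list of tests of difference. A reader might infer that the plan runs at an error rate of about 8%. The documents do not support that as a fact. The figure needs a non-inferiority test at the look, half the information and one-sided 0.05. At one-sided 0.025 it is 4.2%, and if stopping is only for harm or futility there is no increase. This part of the objection stands, and the error rate is stated only conditionally.

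A reader might also infer that the look is uninformative however it is timed, or that giving it up costs nothing because no patient could be spared surgery. Both go too far. At 102 outcomes the look holds half the planned information. At half of enrolment 102 patients remain to be allocated, and the 7–10 day and 3-month assessments could show early harm.

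It is also fair that a definition of half-way, a boundary or an alpha split may stand in the full protocol or analysis plan, neither of which is shown. Their absence is not counted here. A later definition could choose among the three timings, but the limits of each follow from the recruitment period and the follow-up length.

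Lastly, the article does not say that results are shown by arm, so loss of the assessor's blind is a risk the wording leaves open and not a stated plan.

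**Conclusion.** The point holds in this form. The article gives interim results and the termination decision to a committee that includes the assessor who must stay blinded, although an independent-sounding monitoring committee is already provided for. On the protocol's dates and even accrual, half-way means no 12-month outcomes, at most about 15 with 189 to 204 of 204 already enrolled, or 102 outcomes and about 4 recurrences once recruitment has been closed for 5 to 6 months. None of these supports an early non-inferiority decision that would be both grounded in primary data and of use to patients still to be recruited. Slower or uneven accrual would shift the counts.

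The error inflation is conditional: 5% to about 8.0%, or 2.5% to about 4.2%, only if non-inferiority is tested unadjusted at half the information. The blinding and timing points do not depend on it.

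**What to change.** Reword {19} and {21b} to say that:

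- the half-way look is a safety and data-quality review by the existing Data Monitoring and Ethics Committee, with its trigger defined;
- there is no test against the 8% margin and no stopping for non-inferiority, so the full alpha is kept for the final analysis;
- by-arm data go only to that committee, and the Steering Committee, including the Study Secretary, receives only pooled data and a recommendation.

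The cost is a change of wording and the loss of the option to stop early for non-inferiority. Early harm signals from the 7–10 day and 3-month assessments can still be acted on, and no patients are added. Keeping an efficacy look with a stated trigger and an adjusted boundary would also protect the error rate, but it would not cure the timing.

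This closes only the interim route to the assessor. The Study Secretary also performs the randomization ({16a}), and the Steering Committee reviews the operative videos ({20c}); those routes need their own safeguard.

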### Methods for additional analyses (e.g., subgroup analyses) {20b}

No additional analyses will be made.

### Methods in analysis to handle protocol non-adherence and any statistical methods to handle missing data {20c}

Most important stages of the surgical procedures will be recorded to make sure proper technique was applied. Video files will be sent to a dedicated protected server and files will be named after participant code number. Trial Steering Committee will have access to those files and will evaluate them once a month to make sure no crucial errors in technique are made.

### Plans to give access to the full protocol, participant-level data, and statistical code {31c}

The datasets analyzed during the current study and statistical code are available from the corresponding author on reasonable request, as is the full protocol.

## Oversight and monitoring

### Composition of the coordinating center and trial steering committee {5d}

Study Secretary and Study Chief will be known to participants and will be given their e-mail and phone number to stay in constant contact. Swissmed Hospital is the coordinating center as a founder of the trial and serves as the main hub for overseeing the trial operations. Its roles and responsibilities:

1. Oversee the day-to-day operations of the trial.

2. Coordinate with participating centers for patient recruitment and data collection.

3. Ensure that the trial adheres to the protocol and regulatory requirements.

4. Address any logistical challenges and provide necessary resources.

Study Chief and Director, along with Study Secretary and two volunteers collaborators, will be forming Trial Steering Committee. Roles and responsibilities of the Trial Steering Committee:

1. Review and guide the overall direction of the trial.

2. Monitor trial progress and ensure objectives are being met.

3. Address any major issues or challenges faced during the trial.

4. Review and approve major changes to the protocol.

Trial Steering Committee will meet quarterly to review trial progress, and additional meetings can be scheduled if pressing issues arise.

Study group will also have access to WhatsApp group and Facebook closed group to exchange comments/observations and provide organizational support. Study Chief, Study Director, and Study Secretary will be available to all study participants and other collaborators 24/7. Data will be managed by each surgeon designated from collaborator centers. All designated surgeons will form data management team. Data management team will ensure the integrity and security of the trial data. The group will also play a role in assisting in the day-to-day functioning of the trial (logical support, patients management).

### Composition of the data monitoring committee, its role and reporting structure {21a}

Despite trial being a low-risk intervention, the Data Monitoring and Ethics Committee will convene biannually, or more frequently if emergent issues arise, to review trial conduct and ensure the safety and well-being of participants.

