## Methods: participants, interventions, and outcomes

### Study setting {9}

Eleven large surgery centers in Poland, proficient in laparoendoscopic groin hernia repairs (performing at least 80 TAPP/TEP procedures a year), were selected for this study (Table 1 and Fig. 1). List of study sites (collaborators) is given in the Organizational Structure and Responsibilities section at the end of document. Recurrence rate in 12-month follow-up was set as a primary outcome. Swissmed Hospital in Gdańsk, Poland, is responsible for the coordination of MEFI Trial, as well as, for conducting the phone call follow-up protocol. Also, it is the central point of contact for study participants and surgeons. Study participants will be recruited in collaborating hospitals and in coordinating unit. Study Secretary and Study Chief will be known to participants and they will be given their e-mail and phone number to stay in constant contact. Study Chief and Study Director along with Study Secretary and two volunteers from collaborators centers will be form the Trial Steering Committee. The Trial Steering Committee will meet once a month to exchange information and evaluate recent data. Study group will also have access to WhatsApp group and Facebook closed group to exchange comments/observations and provide organizational support. Study Chief, Study Director, and Study Secretary will be available to all study participants and other collaborators 24/7. Data will be managed by each surgeon designated from collaborators centers. All designated surgeons will form the Data Management Team.

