### Plans for communicating important protocol amendments to relevant parties (e.g., trial participants, ethical committees) {25}

Any modifications made to the protocol after its original acceptance will be submitted to Bioethics Committee in District Health Center in Gdańsk and have to be approved by the Steering Committee and Collaborators. Modification and new information will be communicated to the included participants.

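### Interim results and the stopping decision go to a Steering Committee of trial staff that also approves protocol changes; the Data Monitoring and Ethics Committee has no stated part in either

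*Protocol article*

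**What the plan says.** The protocol article spreads oversight over several sections.

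- **Data monitoring committee {21a}.** A Data Monitoring and Ethics Committee meets twice a year, or more often if needed, "to review trial conduct and ensure the safety and well-being of participants". The section says nothing about what data it receives, what it may recommend or to whom it reports.
- **Interim analyses {21b}.** "Trial Steering Committee will have access to interim results and make the final decision to terminate the trial". The timing is given as: "Interim analysis will take place in half-way of the trial". Data management {19} repeats both statements. Neither section mentions the monitoring committee.
- **Data management {19}.** "Only study investigators will have access to trial information and dataset". No exception is made for the monitoring committee.
- **Study setting {9} and Composition {5d}.** The Steering Committee is the Study Chief, the Study Director, the Study Secretary and two collaborators. Study setting {9} adds: "The Trial Steering Committee will meet once a month to exchange information and evaluate recent data".
- **Who will be blinded {17a}.** The Study Secretary, who makes the follow-up calls, is blinded to the method used.
- **Composition {5d}, fourth responsibility of the Steering Committee.** "Review and approve major changes to the protocol".
- **Protocol amendments {25}.** Modifications are submitted to the Bioethics Committee and "have to be approved by the Steering Committee and Collaborators".

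**The concern.** Two things that are normally kept apart sit with the same five people: knowledge of the accumulating comparison and authority over the design. If the Steering Committee sees results by arm and afterwards approves a change to the margin, the sample size, the exclusions or the follow-up, nobody can show later that the change was made without regard to the way the result was leaning. That matters for a non-inferiority claim that the sponsor intends to use to change international guidelines.

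The composition adds a second difficulty. The Study Secretary is the blinded assessor at 3 and 12 months and also a member of the committee that receives the interim results.

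The third is safety. The experimental arm omits a fixation that the Background describes as strongly recommended for these defects, so an excess of recurrences in that arm is the harm to watch for. The committee charged with safety is given no stated route to see it or to advise on stopping.

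**Working it through.** **1. The sections side by side**

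| Function | Steering Committee | Data Monitoring and Ethics Committee | Bioethics Committee |
|---|---|---|---|
| Sees interim results | Yes ({19}, {21b}) | Not stated; outside {19} if read literally | Not stated |
| Decides termination | Yes, final decision ({19}, {21b}) | No role stated | No role stated |
| Approves protocol changes | Yes ({5d}, {25}) | No role stated | Receives them ({25}) |
| Charged with participant safety | Not listed among its four duties ({5d}) | Yes ({21a}) | Not stated |

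Only the Steering Committee combines the first three rows.

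**2. Are the interim results by arm?** The text does not say so. The inference rests on use: the results are tied to a decision to terminate a trial of two arms, and pooled recurrences alone cannot show whether one arm is doing worse. No sentence limits the committee to pooled data. Its members also review operation videos filed under participant code ({20c}), and the recorded stages include placing the mesh ({11a}). They can therefore learn the allocation of coded participants, although the videos by themselves reveal no outcomes.

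**3. The monitoring committee's access.** If its members are not investigators, the access sentence in {19}, read literally, leaves them without data. If they are investigators, they are not independent. The article does not say which applies.

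**4. How much would the half-way split tell its reader?** The separation of roles does not depend on any number; this step only sizes the information.

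Inputs from the protocol: 204 patients randomised 1:1, 10% loss, 4% recurrence, threshold 8%.

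Assumptions: the threshold is an absolute difference of 8 percentage points; half-way means half of the evaluable patients with complete 12-month outcomes; the remaining patients recur at 4% in both arms; the final criterion is a Wald upper bound. The protocol gives a significance level of 0.05 without saying whether it is one-sided, so both readings are shown.

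- Evaluable: 204 × 0.9 / 2 = 91.8, taken as 92 per arm; half-way 46 per arm.
- Expected events at half-way: 2 × 46 × 0.04 = 3.7, taken as 4.
- Final criterion: (p_E − p_C) + z × √[p_E(1 − p_E)/92 + p_C(1 − p_C)/92] < 0.08.
- For each split, 46 further patients per arm are added as independent Binomial(46, 0.04) counts, and the probability of meeting the criterion is summed exactly.

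The probability of each split, given four events and equal rates, is Binomial(4, 0.5).

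| Events at half-way, experimental v control | Probability of split | Final non-inferiority, one-sided 5% | One-sided 2.5% |
|---|---|---|---|
| 0 v 4 | 6% | 99.9% | 99.7% |
| 2 v 2 | 38% | 93% | 84% |
| 3 v 1 | 25% | 73% | 54% |
| 4 v 0 | 6% | 35% | 17% |
| Before any data | – | 87% | 79% |

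The commonest split moves the outlook by about 6 points (87% to 93%) or 5 points (79% to 84%). A 3 v 1 split lowers it by 14 or 25 points. Only the rare 4 v 0 split makes failure more likely than success on both readings.

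**The case against.** **The article is silent on the monitoring committee; it does not exclude it.** Its section is a single sentence, and membership, reports and recommendations commonly sit in a charter or the full protocol. A reader might infer that this committee is barred from the data and has no say in stopping. The documents do not support that. The access sentence is a general confidentiality line, already qualified by the consent provisions {26b}, which foresee sharing relevant data with universities and regulatory authorities. A final decision by the Steering Committee is also compatible with a recommendation from the monitoring committee. This objection stands, and the point claims only that no part is stated. What is stated, twice, is that the Steering Committee sees the interim results and decides.

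**Results by arm are inferred.** This is correct. The inference is strong because the results serve a termination decision, but evaluating recent data at monthly meetings need not mean comparative data.

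**There is an outside check on amendments.** Submission to the Bioethics Committee is a real safeguard. It is partial, because that body is given no interim data and so cannot tell whether a proposed change follows the emerging result.

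**Expecting equal recurrence is the premise of a non-inferiority trial.** Agreed; it is not evidence of bias, and the point does not rely on it.

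**No amendment after the interim look is foreseen.** This is true. The difficulty is that, if one were made, its independence could not be demonstrated.

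**The figures assume outcomes that may not exist while recruitment is open.** Recruitment runs from February 2023 to February–March 2024. With even accrual (an assumption), half of the 12-month outcomes arrive around August–September 2024, after recruitment has closed. An interim look at mid-recruitment would have no 12-month outcomes, though earlier recurrences could be known. This limits the arithmetic to an illustration. A reader might also infer from it that the half-way split all but settles the verdict; the table shows that it does not.

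**Conclusion.** The point holds as a weakness in how stated roles are allocated. The protocol gives interim results and termination to a committee of trial staff that includes the blinded outcome assessor and approves amendments. It gives the existing safety committee no stated part in either. It does not follow that no independent body can ever see harms by arm, because the article does not settle what the monitoring committee receives.

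The conclusion rests on one inference, that interim results used to decide termination are comparative, and on the absence of any restriction to pooled data. The conditional probabilities, from 99.9% down to 35% at one-sided 5% across four-event splits, show that the information is enough to matter to someone who can still approve changes, but is not decisive. They depend on complete 12-month outcomes at half-way, 4% recurrence thereafter and the assumed Wald criterion. The change should be made: it is inexpensive and removes an avoidable challenge to the result.

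**What to change.** 1. **Data management {19}, Interim analyses {21b} and Data monitoring committee {21a}:** state that interim and safety results by arm go only to the existing Data Monitoring and Ethics Committee, in a closed report at the interim look and at its twice-yearly meetings. Add this committee as an exception to the sentence restricting access to investigators.
2. **Same sections:** state that the monitoring committee issues a recommendation, and that the Steering Committee makes its decision on that recommendation plus data pooled over arms.
3. **Composition {5d} and Protocol amendments {25}:** state that those who approve protocol changes have not seen results by arm. Keep the submission to the Bioethics Committee.

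The cost is wording in five sections and a short closed report. The committee already exists, and no patients or visits are added. The downside is small: the Steering Committee gives up sight of results by arm while the trial runs. That also keeps the interim comparison away from the Study Secretary.
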